## Methodology

### Study design

This study employs a mixed methodology in two-prongs. The first prong uses two quasi-experimental methods of a difference-in-differences (DID) analysis and propensity score matching (PSM) technique to analyze Demographic and Health Survey data sets of Ghana 2008/2014 and Kenya 2008/2014. Thus, the 2008 data set for the two countries forms the baseline data, while, the 2014 DHS data sets of countries, represents the end line data set.

The DID method necessarily requires comparable data sets from a different country, other than Ghana, that had not implemented the intervention (the 'free' policy) at the time, hence Kenya. The rationale for choosing Kenya is further explained below and will allow for comparison using data from a non-intervention country at the time, but with similar timelines data sets from DHS. This is also necessary for testing the parallel trend assumption applied in DID.

The propensity score matching (PSM) technique will also be used to estimate the average treatment effect on the treated through the generation of the propensity scores of the two groups; the treated group, post-intervention (2014 DHS) and the untreated group, pre-intervention data (2008 DHS) for comparison using the observed characteristics. The study then assumes that the unobserved characteristics are similar and cancels out, applicable in PSM.

The second prong of the study employs an intrinsic care study design to effect, collecting primary data through one-on-one in-depth interviews, and focus group discussion techniques from the Upper East Region of Ghana for analysis. Inductive thematic analysis will guide the management of the qualitative data using INVIVO 12, with vivid quotations to convey participants’ impressions.

The mixed-method design is driven by the overarching goal of the study; first to measure the free maternal healthcare policy effect on maternal healthcare utilization and to determine the impact of the utilization on stillbirth, perinatal death, and neonatal mortality.

Secondly, the study aims to explore an in-depth understanding of the policy in practice under its current operational constraints to explain policy workability from user and service provider perspectives. Figure 3, presents the diagrammatical representation of the study design.

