Essentially, the ‘free’ policy lacked an operational framework for implementation, but had a political directive that ensured that every pregnant woman gets to register with the national health insurance scheme (NHIS), without paying a premium, and then access comprehensive maternal healthcare free of charge from NHIS accredited health service providers up to 90 days post-delivery [25, 27].

The government of Ghana has since invested several millions of Ghana cedis in a bid to keep the policy running amidst NHIS reimbursement challenges. With nearly 3million women benefitting from the ‘free’ package as by 2013 [28, 29], studies are yet to report on the policy gains or otherwise relative to perinatal healthcare outcome.

Despite the huge financial investment on the free policy intervention, literature is rather restricted to reporting on a nominal increase in attendance at healthcare facilities regardless of time-variant factors and somewhat monotonously on factors that affect the implementation process. Moreover, the existing literature turns to focus more on the policy effects on mothers and less on the unborn and the newborn.

Thus far, the ‘free’ maternal health care policy relationship with maternal healthcare utilization and outcomes, vis a vis medium to long term impact on perinatal healthcare has yet to be adequately documented [30–32].

Incidentally, perinatal death is also poorly researched in Ghana and Sub-Saharan Africa despite its economic burdening abilities [11, 14]. Stillbirth which accounts for a large portion of perinatal deaths has been estimated to have dire consequences on household healthcare expenditure, particularly in areas where the ratios are considered worse than child mortality due to malaria and HIV/AIDS [33–35].

This notwithstanding, perinatal deaths continue to receive little attention in public health and policy research [36, 37]. Hence, this current study seeks to examine the ‘free’ policy effect on maternal healthcare utilization after a decade of implementation and to measures its contributions towards the reduction of stillbirth, perinatal deaths, and neonatal mortality in Ghana.

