## The free maternal healthcare policy in Ghana

The FMHCP was introduced in Ghana through a political declaration in July 2008 by the government of Ghana, with no prior policy framework. Thus, the Ministry of Health (MOH) was tasked to ensure the successful implementation of the policy through the NHIS, an agency under the MOH. In principle, the MOH was tasked to enable the free registration of clinically confirmed pregnant women to access care from NHIS accredited facilities without paying out of pocket.

The policy had no sustainable funding source at the time but relied on an initial £42.5 million ($54.2 million) pledge from the UK government [53]. No clear cut eligibility criteria existed. One needed to be confirmed pregnant by a registered nurse, midwife, or doctor to be enrolled in the national health insurance scheme (NHIS) in the nearest office.

Between 2008 and 2014, the police had registered around 3 million women who benefited from comprehensive maternal healthcare in Ghana at no cost to them, but to the NHIS [28, 54]. With no premium payment, the NHIS appears short-circuited in terms of funding and perhaps, would have to rely on other sources, conventional or otherwise, to fund the ‘free’ policy.

Unsurprisingly, the insurance scheme has since reported funding deficit since the policy implementation characterized by erratic payment of service provider claims, which is copiously documented [47, 55–57]. The slow pace of reimbursement coupled with NHIS card issuance difficulties has created a situation of uncertainty surrounding the implementation of the ‘free’ policy [58].

It is in this light that, this study will seek to explore the current situation of the policy implementation by collecting in-depth primary data from the field of implementation i.e. hospital, clinic, and the policy users to situate the discussions of this study into proper context. Figure 2 presents the number of pregnant women beneficiaries of the policy, while Table 1, below show the proportional changes over the years, indicating inconsistencies in the trend.

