### Statistical methods and rationale

The design and intentions of the ‘free’ policy could not allow for randomization, the gold standard for impact evaluation, hence, quasi-experimental methods; DID and PSM techniques are adopted for the analysis of the secondary data sets. These methods are considered appropriate in evaluating public health programs that have no randomization in the policy design and implementation stages, and in particular, suitable for policies whose choice of participation is somewhat open and voluntary.

Combining the two methods gives the advantage of one making up for the limitations posed by the other. The DID analysis will employ the 2008 data sets of the two countries as baseline data (the starting time), whereas the 2014 DHS data sets of the same will represent the end line (the end time), as shown in Table 2.

**Table 2 Tab2:** Difference-in-differences method

	Before treatment	After treatment	Difference
Treatment (T)	X_0_	Y_0_	T = Y_0_–X_0_
Comparison (C)	X_1_	Y_1_	C = Y_1_–X_1_
Difference	X_0_–X_1_	Y_0_–Y_1_	DD = (Y_0_–X_0_) – (Y_1_–X_1_) = T-C

The choice of propensity score matching technique is also appropriate for the estimation of the policy average treatment effect through the generation of comparators ex-post. A drawback of PSM is the risk of lack of common support for paring treated units to the untreated. This particularly occurs when the sample size is small, so-called the curse of dimensionality. However, this study will merge the 2008/2014 data sets to increase the sample size and to minimize the risk of the curse of dimensionality [49].

Increased sample size will also enhance the study power for precision, albeit, also determined in the original two-stage DHS sampling design. The combined effect of the two quasi-techniques will eliminate the limitation of one and enhance the robustness of the study results [64, 65].

From Table 2 above, before treatment (baseline) is represented be GDHS 2008 (X_0_) for the treatment, T, and KDHS 2008 (X_1_) for the comparison group, C. The after treatment (end line) is also represented by Y_0_ and Y_1_ for Ghana DHS 2014 and Kenya DHS 2014, respectively. Thus, the DID analysis is the difference of T = (y_0_–x_0_) and C = (y_1_–x_1_); estimate for the before treatment difference and the after-treatment difference. The differences between the two represent the treatment effect, thus, the treatment effect is = (y_0_–*x*_*0*_) − (y_1_–*x*_1_), which is equal to T-C.

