### Demographic and health survey data

Demographic and Health Survey data sets are a household survey collected using a two-stage sampling method. Clusters for the sampling in Ghana used sampling frames of the 2000 and 2010 population and housing census to sample for the 2008 and 2014 DHS surveys respectively. For 2008, 412 clusters were determined in the first stage. In the second stage, 29 households were selected from each of the 412 clusters. Household from one cluster data was left out due to ethnic conflict at the time, thus 12, 323 households were selected.

The 2014 DHS also determined 427 clusters; 216 urban areas and 211 rural areas. The second stage then sampled 30 households per cluster for questionnaire administration in each household, thus, 12,831 households, similar to the sampling technique for the 2008 DHS.

In both situations, women between the ages of 15 and 49, who were either permanent residents in the selected households or stayed in the household the night before the selection were eligible to participate in the study and had their blood pressure measured. Sampling excluded women living in barracks, hotels, and prisons. Children between 0 and 59 months were also eligible and had their height and weight checked.

Eligible women participated in the study and answered questions on; age, pregnancy status, education, and relationship to the household head, residence, birth history, parity, pregnancy outcomes, knowledge and use of family planning methods, malaria interventions, diarrheal diseases, antenatal care and facility, and facility delivery (children born within the last 5 years).

Whereas GDHS 2008 collected data on the NHIS, the GDHS 2014 collected information on the free maternal health policy. Ghana and Kenya DHS surveys are similar in sampling procedures and methods and therefore comparable. DHS surveys are considered alternative to population and housing census in many situations due to their wide range of coverage in public health and socio-economic variables.

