Logistics regression is considered appropriate, giving the binary status variables of interest; antenatal care up-take [yes = 1 (ANC visit ≥ 4)] and [no = 0 (ANC visit of ≤ 3]; facility delivery utilization [yes = 1 (facility delivery) and no = 0 (home delivery)], and the secondary outcome variables; stillbirth, perinatal and neonatal deaths, generated through the re-coding of the relevant variable *m14, m15, b6, b7*, and *s1015,* from the DHS data sets (Table 5).

The treatment difference will be determined through nearest-neighbor matching of treated and untreated units’ propensity scores generated ex-post, and using logistics regression while controlling for the confounding variables for precision. The 'free' policy impact will then be determined using the average treatment effect on the treated. Robustness of results will be achieved with reduced standard errors using bootstrapping replication while testing for sensitivity using a t-test of bias, and probit regression.

Of the treatment and comparison country analysis, the DID analysis will be used to determine the policy impact, using the 2008 data set of the two countries (Ghana and Kenya) as a baseline and 2014 data sets as the end line. The study is powered by the sample size calculation, originally determined by the survey design. The sample size is n = 2992/5884 (8,876) for Ghana DHS 2008/2014 data sets, and n = 6079/20,964 (27,043) for Kenya DHS 2008/2014 data sets respectively.

Clustering and stratification will be adjusted for using sample survey weighting at all stages of the analysis. This will produce unbiased treatment estimate that can be generalized to the original survey population [26, 52].

The qualitative data will be deductively analyzed using predefined themes. However, common themes that emerges from the interviews and focused discussion will be organized as sub-themes and inductively reported. The approach will be aided by NVIVO 12, through which nodes and their children will be created to categories significant statements into similarities and dissimilarities [73].

The results of the primary data will be reported using the common themes approach with word frequency count and cloud, and vivid quotations to back themes. The inclusion of qualitative data will add context and situate the discussion with explanatory power to the statistical findings [48].

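### Before and after are set by survey round, not date of birth, so Ghanaian births after the July 2008 launch can fall in the untreated baseline and pull the estimated effect towards zero

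*Protocol article*

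**What the plan says.** The section on the free policy dates the launch: "The FMHCP was introduced in Ghana through a political declaration in July 2008".

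The allocation rule appears in three places, always by survey round:

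- Study design: "the 2008 data set for the two countries forms the baseline data, while, the 2014 DHS data sets of countries, represents the end line data". The same section makes the 2008 DHS the untreated group for the matching and describes it as pre-intervention data.
- Statistical methods and rationale, explaining cell X0 of Table 2: "before treatment (baseline) is represented be GDHS 2008".
- Data analysis: the policy impact is to be determined "using the 2008 data set of the two countries (Ghana and Kenya) as a baseline and 2014 data sets as the end line".

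The section on the Demographic and Health Survey data shows which births are covered. Women answered questions on "antenatal care and facility, and facility delivery (children born within the last 5 years".

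No cut-off by date of birth is given. The variables named for recoding in Table 5 and Data analysis (m14, m15, b6, b7, s1015) include neither a birth date nor an interview date. No fieldwork months are given for any round.

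**The concern.** The launch falls inside the calendar year of the baseline survey, and each record is a birth at some point in the five years before interview. A woman interviewed in Ghana after July 2008 may therefore report a birth that took place under the policy. The round-based rule counts that birth as untreated.

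Both quasi-experimental methods are affected. In the difference-in-differences, exposed births raise X0 and shrink T = Y0 − X0. In the matching, they enter the pool from which untreated comparators are drawn. The causal reading of both methods requires the 2008 Ghana births to be unexposed, and the stated rule does not secure that.

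Pregnancies under way in July 2008 are a related difficulty. Their early antenatal visits came before the launch and their delivery after it, so they are neither fully exposed nor fully unexposed.

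**Working it through.** **Inputs from the protocol article**

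- Launch: July 2008, taken as 1 July.
- Recall window: W = 60 months before interview.
- Ghana sample: 2,992 (2008) and 5,884 (2014), from Data source and size.
- Kenya treated as having no such policy in the period, from the section on Kenya as comparison country.

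**Assumptions, because the article is silent**

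- Births spread evenly over the 60 months.
- A constant effect D, complete from the day of launch.
- Ghana 2008 fieldwork finished by the end of 2008.
- Each of the 2,992 records is one birth, unweighted.

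**Step 1: the article's own figure.** 2,992 + 5,884 = 8,876, which matches the pooled Ghana sample in Data analysis. No power or effect calculation is given that could be rebuilt.

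**Step 2: effect of contamination.** Let f be the share of Ghana 2008 births that fall after launch, G and K the untreated levels in the two countries, and t the common trend.

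- X0 = G + fD and Y0 = G + t + D
- X1 = K and Y1 = K + t
- DID = (Y0 − X0) − (Y1 − X1) = (t + D − fD) − t = D(1 − f)

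The simple 2014-against-2008 contrast behind the matching loses the same fD. Matching changes the weights, so there the result is approximate.

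**Step 3: size of f.** A woman interviewed m months after launch has a share m/60 of her window after launch, or zero if she was interviewed earlier. Over the sample, f is the mean of those months divided by 60.

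| Ghana 2008 interviews (assumed) | Mean months | f | Births of 2,992 | A 10-point effect reads |
|---|---|---|---|---|
| All before launch | 0 | 0% | 0 | 10.0 |
| Spread evenly from launch to month 5 | 2.5 | 2.5/60 = 4.2% | about 125 | 9.6 |
| Spread evenly from launch to end of 2008 | 3 | 3/60 = 5.0% | about 150 | 9.5 |
| All at month 5 | 5 | 5/60 = 8.3% | about 249 | 9.2 |
| All at end of 2008 | 6 | 6/60 = 10.0% | about 299 | 9.0 |

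**Step 4: sensitivity to the window.** If an outcome covered only more recent births, f would rise. With a mean of 3 months it is 3/36 = 8.3% for an assumed 36-month window and 3/24 = 12.5% for an assumed 24-month window. The article states five years, so 60 months is the main case.

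**Step 5: the other cells.** A 2014 round with five-year recall reaches back no further than 2009, so Y0 contains no births from before the launch. Kenya has no exposed births under the article's premise, so X1 and Y1 are unaffected.

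**The case against.** The strongest objection is that the harm depends on a fact the article does not give. If the Ghana 2008 interviews were finished before July 2008, there is no contamination. This stands. A reader might infer that the difference-in-differences certainly is diluted, but the article supports only the conditional statement.

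A reader might also take the last month of fieldwork, divide it by 60, and report about 8% for fieldwork ending five months after launch. That share applies only to women interviewed in the final days. The sample share depends on the mean interval, which gives about 4% if interviews were evenly spread.

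Full effect from day one is also a generous assumption. The article says the policy began without a prior framework, and Table 1 shows 383,216 enrolments for 2008/2009 together against 754,658 in 2012. For four or more antenatal visits, births soon after launch came from pregnancies spent mostly before it. Both points make the likely loss smaller than the table shows.

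A further inference would be that the Kenya baseline or the Ghana end line is contaminated too. Step 5 shows that neither is. The phrase about a decade of implementation in Background is a separate wording matter and adds nothing here.

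Finally, a date filter might be seen as a data-cleaning detail that a condensed article leaves out. This does not answer the point: the article states a round-based rule three times and labels the 2008 round pre-intervention without qualification.

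**Conclusion.** The concern holds in conditional form. The stated rule can place exposed Ghanaian births in X0 and in the untreated group for matching, and under a constant effect any such bias is towards zero. On a 60-month window with full effect from launch, the loss is 0% if all interviews preceded July 2008, about 4% if they were spread evenly over the next five months, and at most about 10% if all took place at the end of 2008. The upper limit rests on fieldwork ending within 2008 and on the five-year window. Gradual take-up and partly exposed pregnancies would lower it; a shorter window would raise it.

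The effect is modest and would not by itself overturn a large finding. It is still worth correcting before analysis, because the baseline is described as untreated and the stated rule does not make it so.

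**What to change.** 1. State the fieldwork months of the Ghana 2008 survey.
2. In the Ghana 2008 file, define before as births earlier than July 2008, for both the difference-in-differences and the matching.
3. Apply the same calendar cut-off to the Kenya 2008 file, for symmetry only.
4. Set aside births whose pregnancies straddle the launch, roughly those up to nine months after it. If the 2008 fieldwork ended in that year, these are the same births that step 2 removes. In the 2014 file only the first three months of 2009 could be involved, so almost nothing is lost there.
5. Report the all-births, round-based version as a sensitivity analysis.

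The cost is a few lines of data preparation using birth dates, and a few per cent of baseline births: about 125 of 2,992 in Ghana under the evenly spread five-month case and about 299 at the upper limit. The same 4.2% share in Kenya would be about 253 of 6,079. If fieldwork proves to have preceded the launch, the Ghana result does not change and the baseline assumption has been verified.

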### Kenya as a comparison country

Comparatively, Kenya showed relevant commonalities as Ghana and was chosen as a comparison country. First, Kenya DHS data were collected about the same time as Ghana and had no such intervention within the time frame. This is necessary for the DID analysis.

Secondly, the DHS reports of the two countries show similarities of related variables of interest in this study. For example, Ghana recorded 30 and 50 per 1000 live births for neonatal and infant mortality rates respectively, and within the same period, Kenya also recorded 31 and 52 per 1000 live births for neonatal and infant mortality, according to their respective 2008 DHS reports [59–61].

Also, Kenya was considered appropriate giving its geopolitical and socioeconomic similarities to Ghana such as; political stability, literacy rate, lingua franca, and Sub-Saharan location.

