### Statistical assumptions

The parallel trend assumption guide the use of DID analysis and assumes that no time-varying differences exist between the treatment and comparison groups of both countries. The second critical assumption for the difference in differences method is that the outcomes of interest in the two countries will move in tandem with or without the treatment. The Propensity Score Matching technique on the other hand assumes that, no systematic differences exist in the unobserved characteristics between the treatment group and the comparison group.

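### The planned two-round Ghana–Kenya difference-in-differences cannot test parallel trends as the protocol implies, and the assumption is worded so that the effect would be zero

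*Protocol article*

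**What the plan says.** Under Study design, "the 2008 data set for the two countries forms the baseline data, while, the 2014 DHS data sets of countries, represents the end line data". The same section explains that the DID needs data from a country without the policy, and adds: "This is also necessary for testing the parallel trend assumption applied in DID".

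Statistical methods and rationale confirms the two-point structure: "The DID analysis will employ the 2008 data sets of the two countries as baseline data". Table 2 gives the estimator as DD = (Y0 − X0) − (Y1 − X1) = T − C, where X is 2008, Y is 2014, subscript 0 is Ghana and subscript 1 is Kenya. Table 6 lists four data sets for retrieval, none earlier than 2008.

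The section on Kenya as a comparison country rests on 2008 levels ("Ghana recorded 30 and 50 per 1000 live births for neonatal and infant mortality rates", against 31 and 52 in Kenya) and on general similarities between the countries. It gives no trend.

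Statistical assumptions states the identifying condition twice. First, it "assumes that no time-varying differences exist between the treatment and comparison groups of both countries". Second, "the outcomes of interest in the two countries will move in tandem with or without the treatment".

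**The concern.** The article names a test of the DID's key assumption, but the analysis it describes holds no information on how the two countries were moving before July 2008, when the policy began. A report written from this plan could present parallel trends as tested when they had only been assumed.

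Two features of the study add weight. The Background faults earlier work for reporting rises in attendance without regard to factors that change over time, so handling such change is part of what this study offers. And the propensity score matching, as set out under Study design, compares treated units from 2014 with untreated units from 2008. It therefore does not remove change over calendar time. Only the DID tries to, and it succeeds only if parallel trends hold.

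The wording of the assumption is a second, separate error. Parallel trends concern what would have happened without the policy. Extending the condition to the treated state contradicts the purpose of the estimator.

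**Working it through.** **1. Can the planned DID test trends?** The inputs are two countries and two rounds, so four cell means (Table 2). The parameters are a constant, a country term, a period term and country × period (the policy effect).

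- The design matrix has 4 rows and rank 4, so residual degrees of freedom = 4 − 4 = 0.
- Adding a Ghana-specific trend gives 5 parameters and the rank stays 4. With two time points, the trend column is identical to the policy-effect column.
- With one more pre-policy round per country there would be 6 cells, 6 parameters and rank 6, and the differential linear trend would become estimable. No such round is listed.

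Example with assumed cells: Ghana 60% to 75%, Kenya 45% to 55%. DD = 15 − 10 = 5 points. The same four cells fit a policy effect of +10, +5, 0 or −5 points if the differential trend over the period is −5, 0, +5 or +10 points.

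**2. Does the Kenya comparison fill the gap?** The figures 30 against 31 and 50 against 52 per 1000 are levels at one time. Equal levels are compatible with any pair of slopes.

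**3. What does the stated assumption imply?** If outcomes move in tandem with the treatment, Y0 − X0 = Y1 − X1. In the protocol's own formula, DD = (Y0 − X0) − (Y1 − X1) = 0.

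**4. Size of the possible error (ANC uptake and facility delivery only).** The sample sizes come from Data source and size: Ghana 2992 and 5884, Kenya 6079 and 20,964. The assumptions are 50% prevalence, a design effect of 1 or 3, and a trend difference of 1 or 0.5 point per year. The documents give none of these.

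- SE(DD) = √[0.25 × (1/2992 + 1/5884 + 1/6079 + 1/20,964)] = 0.0134, or 1.34 points. With design effect 3: 1.34 × √3 = 2.32 points.
- 1 point per year over 6 years gives 6 spurious points: z = 6/1.34 = 4.48 (6/2.32 = 2.59). A policy with no effect would be declared significant 99% (74%) of the time.
- 0.5 point per year gives 3 spurious points: 61% (25%).

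These figures do not carry over to deaths. Six points is 60 per 1000, twice Ghana's quoted neonatal rate of 30 per 1000.

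**5. How informative would a birth-year check be?** Demographic and health survey data lists, among the items asked, "facility delivery (children born within the last 5 years". I assume births spread evenly over 5 years (variance of birth time 25/12 = 2.083), all 2008-file births falling before the policy, and 50% prevalence.

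- SE of the difference in slopes = √[0.25/(2992 × 2.083) + 0.25/(6079 × 2.083)] = 0.0077, or about 0.77 point per year. With design effect 3: 1.34.
- Power for 1 point per year: about 25% (12%).
- Projecting the slope over 6 years adds an SE of 6 × 0.77 ≈ 4.6 points (6 × 1.34 ≈ 8.0), against 1.34 (2.32) for the DID itself.

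**The case against.** The quoted sentence says that comparison-country data are necessary for the test, not that two rounds are sufficient. The data are individual child records covering about five years of births, so the four-mean argument applies to the planned summary and not to the files. A condensed article may also leave the method of a test to the full protocol or analysis plan.

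The point about the records stands. A reader might infer that these data cannot inform parallel trends at all. The documents do not support that, because the 2008 children files could be split by birth year. But the article describes each country's 2008 data as one baseline point and gives no birth-year step. The finding is not that detail is missing. The article attaches a testing claim to an analysis that cannot deliver the test.

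On the wording of the assumption, it can fairly be said that no analysis step uses the phrase, that Table 2 is correct, and that the Expected outcome section anticipates a positive effect. That also stands: no estimate changes. The sentence still defines identification wrongly and should be corrected.

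A reader might also take the DID to be the main causal estimate. The article gives no such ranking. It presents DID and matching together, and Data analysis uses both to determine policy impact.

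**Conclusion.** The point holds for the DID as planned. With one baseline and one end-line value per country, parallel trends are assumed and not tested, and a differential trend is indistinguishable from the policy effect. This follows from the structure of Table 2 and needs no numerical assumption. The second statement of the assumption is also wrong as written, because it forces T − C to zero.

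The magnitudes are illustrative. The rejection rates of 99% (74%) and 61% (25%) rest on assumed trend differences, 50% prevalence and, in brackets, an assumed design effect of 3. They apply to ANC uptake and facility delivery, and no usable size is given for stillbirth, perinatal or neonatal death. They show what would follow from a trend difference. Nothing in the documents shows that Ghana and Kenya were in fact diverging, so the inference that the estimate is biased is not supported.

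The article should be corrected on both points. The identification argument is firm; the size of any bias is unknown.

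**What to change.** 1. In Statistical assumptions, replace both statements with one: absent the policy, the Ghana–Kenya difference in each outcome would have stayed constant from 2008 to 2014.

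2. Then choose one of two courses.
   - **Examine pre-policy trends.** Fit country-by-birth-year terms to births before July 2008 in the 2008 children files, for each outcome where it is recorded. Show the estimates with confidence intervals, and state in advance that a non-significant result does not prove parallel trends. Report a trend-adjusted DID as a sensitivity analysis only.
   - **Withdraw the claim.** Delete the sentence about testing under Study design and report parallel trends as an untested assumption and a limitation.

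3. In either case, present the matching 2008 mortality levels as similarity of levels, not as evidence on trends.

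The first course needs only analysis time, since access to the data sets is already approved. Its drawback is low power: about 25% for a 1 point per year difference at 50% prevalence, or 12% with design effect 3. The trend-adjusted DID would be very imprecise, which is why it should not replace the planned estimate. The second course costs nothing beyond a more cautious claim.
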